**Figure 1 figure1:**

Participant flow through the OKquit study. OTH: Oklahoma Tobacco Helpline; REDCap: Research Electronic Data Capture.

**Figure 2 figure2:**
[figure not shown]
OKquit app home screen by Quit Phase. The red boxes indicate app features that are available only to the OKquit group. Features not in red boxes are available to all participants.

After initial randomization into the study and after clicking the “Set New Quit Date” button during the 27-week study period, all participants move to the Pre-–Quit Phase. Participants remain in the Pre–Quit Phase for up to 21 days (this duration is determined by the participants when they set their quit date). After setting a new quit date, the participants gain access to an app home screen that provides free smoking cessation resources including a one-click call to the OTH (both groups) and additional OKquit app resources (OKquit group only; see Figure 2). Instructions for phase-specific features are available for review at any time via the “App Instructions” button on the app home screen. During the Post–Quit Phase, the participants continue to have access to the free smoking cessation resources and additional OKquit app features through the Post–Quit Phase home screen (see Figure 2). On the morning of the quit date, the participants are prompted to complete a quit date assessment and are provided instructions about the Post–Quit Phase app features. In this phase, the participants complete up to 6 brief daily check-ins, a weekly survey, and are asked to complete slip assessments if or when they lapse. During the weekly survey, participants are asked whether they have smoked in the past 7 days. Their response to this item determines what phase they will move to next. If the participants report they have not smoked, they are asked, “How LIKELY is it that you will NOT smoke in the NEXT MONTH?” If they respond less than 8 on a 1-10 scale, they remain in the Post–Quit Phase. If they respond 8 or more, they move to the Maintenance Phase. If they report that they have returned to smoking, they are asked, “Right NOW, are you ready to get back on the wagon and set a new quit date within the next 21 days?” If they answer no to this question, they are moved to the Motivation Phase.

During the Maintenance Phase, the participants complete daily check-ins, weekly surveys, and are asked to complete slip assessments if or when they lapse. After reporting a lapse, the participants are asked whether they want to continue the quit attempt. Participants who choose to end their quit attempt are moved to the Motivation Phase. Those that choose to continue the quit attempt remain in the Maintenance Phase. In addition, all participants can click the “Set New Quit Date” button on the app home screen to change their quit date or set a new quit date at any time. Finally, during the weekly survey, the participants are asked whether they smoked within the past 7 days. If they indicate that they have smoked, they are asked whether they are ready to set a new quit date. Participants who choose a new quit date are moved back into the Pre–Quit Phase or the Post–Quit Phase. Participants move into the Motivation Phase when they report a lapse and want to end their quit attempt. Motivation Phase participants who use the “Set New Quit Date” button to set a quit date move to the Pre–Quit Phase or the Post–Quit Phase.

### Study Conditions

Those who are eligible and enroll in the study are randomly assigned to 1 of 2 conditions: Standard OTH Care (SC) or SC plus the OKquit intervention.

### Standard OTH Care (SC) Condition

Standard OTH services, including NRT (eg, nicotine patches, gum, and lozenges), phone-based counseling, and web-based intervention services are available to all participants. SC participants are prompted to complete brief daily check-ins and weekly surveys through the Insight app. In addition, SC participants have access to an on-demand one-click “Call Oklahoma Helpline” feature in their app. SC participants are able to advance through the 4 PBM phases (ie, Motivation, Pre–Quit, Post–Quit, and Maintenance); however, they do not receive tailored messages after each weekly survey or daily check-in. Instead, SC participants receive “factoid” or trivia-type messages at the completion of each check-in or weekly survey. These factoid messages serve as an attention control (see Table 1).

**Table 1 table1:** Message types and examples.

Message level	Phase/group	Example
1	Motivation (OKquit)	First name, after quitting smoking, ex-smokers report lower levels of stress than when they were smokers.
2	Pre-Quit (OKquit)	First name, after you quit smoking, you will be tempted to lapse. Reduce temptation by removing ashtrays, lighters, matches, and cigarette butts. These items can trigger cravings and reduce motivation for staying quit.
3	Post-Quit: Low Risk for Imminent Lapse (OKquit)	First name, sometimes people save a pack of cigarettes (or even a few cigarettes) “just in case” or to prove they have the willpower to not smoke. DON’T! This just makes it easier to start smoking again!
4a: Stress	Post-Quit/Maintenance: High Risk for Imminent Lapse (OKquit)	First name, right now, it may feel like smoking would be enjoyable. However, you will feel worse later on if you do smoke now. You can get through this time without smoking.
4b: Urge	Post-Quit/Maintenance: High Risk for Imminent Lapse (OKquit)	First name, when you crave a cigarette, focus on a happy memory and get away from it all for a moment. Concentrate on that memory and nothing else.
4c: Cigarette Availability	Post-Quit/Maintenance: High Risk for Imminent Lapse (OKquit)	First name, you may be tempted to smoke when you see someone smoking or smell smoke. Do something to keep your mind off smoking. Listen to music, read, call a supportive friend, or take a walk.
4d: Cessation Motivation	Post-Quit/Maintenance: High Risk for Imminent Lapse (OKquit)	First name, you are setting a great example for children and others in your life! Congratulations on quitting smoking!
5	Maintenance: Low Risk for Imminent Lapse (OKquit)	First name, bored? Consider going to the movies or the mall—smoking is forbidden in most indoor places.
6	Post-Quit Recently Lapsed (OKquit)	First name, most smokers try to quit multiple times before they kick the habit for good, keep on trying!
7	SC^a^	It would take almost 23 million ping pong balls to fill a 747.

^a^SC: standard care.

### OKquit Condition

OKquit participants have access to all SC intervention features and app content and complete the same daily check-ins and weekly surveys as the SC group. However, OKquit participants have access to several additional features (see details in the Automated Messages and On-Demand Content sections).

#### Automated Messages

During each of the daily check-ins and weekly surveys, OKquit participants receive intervention content that is tailored to their current quitting phase (ie, Motivation, Pre-Quit, Post-Quit, and Maintenance; see Figure 2 for screenshots of the OKquit app by study phase), current level of risk for imminent lapse (ie, Cessation and Maintenance Phases only), and currently reported smoking lapse risk factors (ie, Cessation and Maintenance Phases only).

More than 900 unique messages have been embedded into the OKquit app. Messages were taken from a message bank that was developed by this research team and have been evaluated by 6 tobacco experts [27]. Table 1 provides a summary of the various message types, the phases that messages are available or used, along with example messages. All messages begin with the participant’s first name. One message is delivered at the end of each check-in and weekly survey (up to 6 per day). Level 1 messages are presented during the Motivation phase. These messages aim to increase motivation and readiness to quit smoking. Level 2 messages are presented during the Pre–Quit Phase. These messages consist of content that aims to prepare the participants for their upcoming quit attempt. During the Post–Quit and Maintenance Phases, the participants receive personalized automated messages based upon their current risk of imminent smoking (a complete description of the lapse risk estimator is presented elsewhere [23]). When participant responses indicate a low degree of risk for smoking lapse during the Post–Quit Phase, level 3 messages are presented. Level 3 messages provide general coping strategies for lapse triggers that are commonly encountered early in quit attempts. When participants report that they smoked the day prior, or they indicate that they have more than 0% likelihood of smoking that day, level 4 messages are delivered. Level 4 messages provide suggestions on ways participants could cope with 1 of 4 currently experienced smoking lapse triggers (ie, easy access to cigarettes, high stress, high urge, or low motivation for cessation). Level 5 messages are delivered during the Maintenance Phase when the app algorithms indicate low risk for imminent lapse. Level 5 messages provide general advice on sustaining longer-term abstinence. If a participant reports multiple current triggers, 1 message is delivered in this order of priority: easy access to cigarettes, high stress, high urge, or low motivation for cessation. This order is based on findings from our previous research [19,20,23,24]. Specifically, variables that are better at indicating high risk for imminent lapse are given higher priority than variables that are less strongly linked with imminent lapse. When a participant initiates a Slip assessment, a level 6 message is presented at the completion of the assessment. Level 6 messages focus on encouraging participants to resume smoking abstinence.

#### On-Demand Content

OKquit participants have access to various on-demand features available through the smartphone app home screen. The following features are accessible 24 hours a day for 27 study weeks and include (1) the “Quit Tips” button that offers a menu of treatment-related messages, relaxation exercises, and distraction videos, (2) the “Medication Tips” button that provides information about common smoking cessation medications (eg, nicotine gum, patch, and lozenges), such as medication use tips and common medication side effects, and (3) the “Additional Resources” button that provides helpful information and website links to useful resources (eg, COVID-19 tests, food, housing, and job placement resources). When a participant clicks the “Quit Tips” or “Medication Tips” buttons, a menu of options appears (see Figure 3 for menus and example messages).

**Figure 3 figure3:**
[figure not shown]
Quit Tips and Medication Tips Menus and examples available in the OKquit app.

### Measures

#### Overview

The initial prescreener survey is completed via REDCap. The screener collects individual contact information and demographic information (eg, age, race, and biological sex at birth), average cigarettes smoked per day, and level of desire to quit smoking. The baseline assessment (30 minutes), weekly surveys (3-5 minutes each), daily check-ins (10-30 seconds), and 27-week follow-up assessment (20 minutes) are collected via the Insight app. See Table 2 for study assessments and administration schedule. For daily check-ins and weekly surveys, the phone rings and vibrates to prompt the participant to complete the assessment. If the participant does not respond after 5 prompts, the check-in/survey is automatically rescheduled up to 3 times 15 minutes later. Assessments collect information about several factors related to smoking, smoking lapse, and health. Participants are instructed to self-initiate “About to Slip” and “Already Slipped” assessments and to initiate the “Set New Quit Date” assessments when they want to set a new quit date. Each check-in and survey are date-, time-, and geolocation-stamped for future examination.

**Table 2 table2:** List and timeline of study measures.

Measure	Screener	Baseline	Follow-up
Screening Questionnaire	✓		
Phone Call Screener	✓		
Rapid Estimate of Adult Literacy in Medicine—SF (REALM) [25]	✓		
Tobacco History Questionnaire		✓	✓
Heaviness of Smoking Index [28]		✓	✓
Self-Efficacy Scale/Confidence [29]		✓	✓
Demographic/Background Information Questionnaire		✓	
MacArthur Scale of Subjective Social Status [30]		✓	✓
Overall Anxiety Severity and Impairment Scale (OASIS) [31]		✓	✓
Overall Depression Severity and Impairment Scale (ODSIS) [32]		✓	✓
The Patient Health Questionnaire-4 (PHQ-4) [33]		✓	✓
Financial Strain Questionnaire [34]		✓	
Perceived Stress Scale [35]		✓	✓
The Everyday Discrimination Scale (Brief version) [36]		✓	
The Pandemic Stress Index		✓	
Perceived Social Support Questionnaire [37]		✓	
Religious Participation [38,39]		✓	✓
Self-Rated health [40]		✓	✓
Health Related Quality of Life [41]		✓	✓
Alcohol Use Disorders Identification Test (AUDIT-C) [42]		✓	✓
Marijuana/Cannabis Use Behavior		✓	✓
BRFSS Inadequate Sleep [43]		✓	✓
Short Scale of Anxiety Sensitivity Index (SSASI) [44]		✓	✓
Cannabis Use Disorder Identification Test Short Form [45]		✓	✓
Weekly EMA^a^ items		✓	✓
Smoking Status items			✓
System Usability Scale [46]			✓
Treatment Quality and Satisfaction Survey			✓

^a^EMA: ecological momentary assessments.

#### Check-Ins

Thirty minutes after the preset wake time, participants are prompted by the app to complete a morning check-in. The app welcomes participants in each condition with a different message. The SC group is told that the check-in should take less than 30 seconds to complete and given no further instructions. The OKquit group is told that the check-in should take less than 30 seconds and that their answers to the check-in questions will help the app tailor messages to their current needs. All participants are then asked, “How many cigarettes did you smoke yesterday?” OKquit participants in the Post–Quit and Maintenance Phases receive a message reminding them how many days they have been smoke-free and how much money they have saved to date by not smoking. All participants are then asked, “Which of the following apply to you RIGHT NOW? (Check all that apply).” Answer responses include the following: I could easily get cigarettes within 5-10 minutes; someone is currently smoking near me; I feel stressed; I have an urge to smoke; my motivation to quit smoking is low; I drank alcohol in the last hour; and none of the above. Next, participants are asked, “How likely is it that you will smoke between now and the end of the day?” Answer responses range from 0% to 100%. Participants are then asked, “Which of the following brief (30 seconds) check-ins would you like to schedule for today?” with the following responses: 10:00 AM, 12:00 PM, 4:00 PM, 6:00 PM, 1 hour before your usual bedtime, and None of the above. After these questions are completed, SC participants receive a level 7 (ie, factoid) message, and OKquit participants receive a message tailored to their current PBM stage and their current situation. Participants are prompted at the specified times to complete the additional check-ins that they selected for that day.

#### Weekly Survey

All participants are prompted to complete the weekly survey on Saturdays for 27 weeks. The weekly survey includes all items from the morning check-in and additional items about smoking status, current thoughts about quitting, whether they have attempted to quit smoking during the past 7 days, motivation and desire to quit smoking, cessation fatigue, alcohol and drug use, social support, and several additional items. After these questions are completed, SC participants receive a level 7 (ie, factoid) message, and OKquit participants receive a message tailored to their current PBM stage and their current situation.

#### Biochemical Verification of Smoking Status

Participants who report smoking abstinence 26 weeks after enrollment are mailed a Bedfont iCO Smokerlyzer to complete a breath test and verify their smoking status. Step-by-step instructions are presented on the smartphone screen on how to complete an iCO test. All test results are date- and time-stamped and saved for future analysis.

#### OTH Data

OTH will provide the research team with data on all interactions with study participants. In particular, the dates and number of OTH coaching sessions completed will be extracted, along with the dates and amounts of NRT ordered.

### Compensation

Participants receive compensation for completing the baseline assessment (US $20), weekly surveys (US $5 each), and the 27-week follow-up assessment (US $50) via a reloadable GreenPhire Mastercard. Participants are not compensated for completing or accessing treatment components including daily check-ins, on-demand assessments, or intervention content. Participants who report 7-day smoking abstinence at 26 weeks post enrollment (via weekly survey) and provide a breath sample are paid an additional US $20 regardless of their actual smoking status. Thus, participants may receive up to US $225 for completing all study measures. Participants can click the “Payment” button on the app home screen to review their compensation summary.

### Smartphone Programming

The mHealth Shared Resource at the NCI Designated Stephenson Cancer Center provided the smartphone app programming services for this project. This resource employs 9.5 team members including 5.5 computer scientists and engineers who develop and maintain web and mobile apps and relational databases. To date, this resource has supported 94 research studies.

### Statistical Analysis

Descriptive statistics for continuous variables will include mean, SD, and quantiles, and categorical variables will be summarized as percentages and counts. We hypothesize that participants randomly assigned to the OKquit group will have significantly higher rates of biochemically verified 7-day point prevalence smoking abstinence than those assigned to SC at 27 weeks post randomization. We will use a chi-square test or Fisher exact test to compare the proportion of participants in the treatment conditions (ie, OKquit and SC) who are biochemically verified as abstinent (ie, iCO <7 ppm, and self-reports show no smoking in the past 7 days) 27 weeks after randomization. We will conduct the analysis using the intention-to-treat assumption wherein participants who are lost to follow-up or fail to complete the iCO evaluation will be classified as not abstinent. Prior to analyzing the data, we will examine the missing rate and patterns of missing data. If the missing rate is high, then we will explore sequential multiple imputation with at least 20 imputed data files as described by Raghunathan et al [47]. The analysis results from sequential multiple imputation data will be compared with those from the available data and intention-to-treat analyses. Based upon previous studies [48], we expect that 9% of those receiving the SC intervention will be biochemically confirmed abstinent at the 27-week post–quit follow-up, and based upon our pilot work, we expect that 18% of those receiving the OKquit treatment will be abstinent at the 27-week postquit follow-up visit [19,20]. With alpha values of .05 and 250 participants in each group, we have 84% power to detect a 9% difference in biochemically confirmed 7-day point prevalence abstinence at 27 weeks (ie, 45/250, 18% abstinent in the OKquit group vs 22/250, 9% abstinent in the SC group) by using Pearson chi-square test. In addition to the chi-square test or Fisher exact analysis, we will perform logistic regression analyses to determine whether the odds of abstinence vary by other baseline characteristics (eg, sex, race, and ethnicity). Finally, we will examine interactions between treatment condition and sex and race (separately) to identify potential differential effects on abstinence.

We will examine secondary outcome measures from the collected data, including 30-day point prevalence abstinence, days to first lapse, and longest period of abstinence, which will be compared across treatment conditions. We will use the chi-square test or Fisher exact test and logistic regression models to examine 30-day point prevalence abstinence. For time to first lapse, Kaplan Meier and Cox regression modeling methods will be used. For the longest period of abstinence, *t* test or Wilcoxon rank sum test and linear regression methods will be used. Finally, we will use generalized linear mixed model regression analysis to compare abstinence rates between groups over time.

We hypothesize that OTH service engagement and use of OKquit intervention content will predict biochemically verified 7-day point prevalence smoking abstinence 27 weeks post randomization. Logistic regression models will be used to examine whether total number of OTH coaching sessions completed and OTH NRT shipments predict 27-week biochemically confirmed 7-day point prevalence abstinence. We will also examine whether the number and type of interactions with the OKquit app (eg, messages viewed) predict 27-week abstinence. Baseline characteristics such as race and sex will be considered as potential covariates during the modeling process.

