### Procedure

Individuals who contact the OTH for smoking cessation services via the phone or web are asked whether they are interested in participating in a smoking cessation research study. Contact information for interested individuals is shared with OKquit research team members who then send a web-based Research Electronic Data Capture (REDCap) study screener link to these individuals. Those who complete the 5-minute REDCap screener and meet the initial study inclusion criteria then complete an enrollment call, which includes the informed consent process and a full study eligibility assessment. Those who enroll in the study receive instructions about how to download the Insight app onto their personal smartphone, and they are given 7 days to complete the 30-minute app-based baseline survey. Following completion of the baseline survey, research staff contact participants to randomize them into an intervention group. Randomization is stratified based on self-reported race and ethnicity (non-Hispanic White vs minoritized race and ethnicity), biological sex at birth (male vs female), and number of cigarettes smoked per day (20 vs ≥20). During the randomization call, all participants are asked to use the app to select a quit date within the next 21 days, are given instructions on how to access intervention content, and are instructed on how to complete the prompted daily check-ins and weekly surveys. Following randomization, participants interact with their assigned intervention for the 27-week study duration. Those who report abstinence from smoking during the 26th weekly survey are mailed a Bedfont carbon monoxide monitor that pairs with the Insight app by pressing the power button on the device, and they are asked to submit a breath sample for abstinence verification. Participants are also prompted to complete a 27-week follow-up assessment via the Insight app. The study flow is shown in Figure 1.

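### The primary test ignores the randomization strata and leaves chi-square or Fisher open; it is valid, but a single stratified test would be slightly more powerful at no cost

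*Protocol article*

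**What the plan says.** Under Procedure, the protocol article states: "Randomization is stratified based on self-reported race and ethnicity (non-Hispanic White vs minoritized race and ethnicity), biological sex at birth (male vs female". The third factor is "number of cigarettes smoked per day (20 vs ≥20". Three two-level factors give 2 × 2 × 2 = 8 strata.

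Under Statistical Analysis, the primary comparison of verified 7-day abstinence at 27 weeks is: "We will use a chi-square test or Fisher exact test to compare the proportion of participants in the treatment conditions". No stratum or covariate enters this comparison, and no rule says which of the two tests applies. Power is computed for one of them: "With alpha values of .05 and 250 participants in each group, we have 84% power to detect a 9% difference", "by using Pearson chi-square test", with planning rates "45/250, 18% abstinent in the OKquit group vs 22/250, 9% abstinent in the SC group".

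In addition, "we will perform logistic regression analyses to determine whether the odds of abstinence vary by other baseline characteristics". Sex, race and ethnicity are given as examples; cigarettes per day is not. Interactions of treatment with sex and with race follow. None of these models is called the primary or the adjusted treatment comparison.

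On missing outcomes, "participants who are lost to follow-up or fail to complete the iCO evaluation will be classified as not abstinent", so all 500 randomized participants count in the comparison.

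**The concern.** Stratified randomization balances the three factors between arms, which removes part of the chance variation in the difference between arms. The variance in an unadjusted chi-square test still includes the between-stratum variation. If the factors predict abstinence, the standard error is therefore a little too large, and some of the benefit of stratifying is lost on the endpoint that decides the trial.

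The second matter is that two tests are named for one hypothesis. They have different rejection regions, and only one of them matches the power statement. A result near the 5% boundary could count as positive under one and negative under the other.

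**Working it through.** **Inputs from the protocol article:** 250 per arm, alpha 0.05, rates 18% and 9%, Pearson chi-square, eight strata. Sidedness is not stated.

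**1. Reproducing the stated power.** Pooled rate: (0.18 + 0.09)/2 = 0.135.
- SE under the null: √(2 × 0.135 × 0.865/250) = 0.03056.
- SE under the alternative: √(0.18 × 0.82/250 + 0.09 × 0.91/250) = 0.03030.
- z = (0.09 − 1.960 × 0.03056)/0.03030 = 0.993, so power = Φ(0.993) = 0.840.

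The stated 84% is reproduced by the two-sided Pearson test without continuity correction. A one-sided test would give 0.905.

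**2. Pearson against Fisher.** Exact enumeration of all pairs of binomial counts, 250 per arm:

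| Test | Power, 18% vs 9% | Size, both arms 9% |
|---|---|---|
| Pearson | 84.6% | 4.9% |
| Fisher | 81.5% | 3.5% |

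Under the planning rates the two tests disagree in 3.1% of trials, and in every such case Pearson rejects and Fisher does not. One example, keeping 22/250 in standard care: 37/250 in OKquit gives Pearson p = 0.038 and Fisher p = 0.052.

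**3. Is Fisher needed?** With 45 + 22 = 67 abstainers, the smallest expected cell is 67/2 = 33.5. An expected cell below 5 would need fewer than 10 abstainers among 500. Even 9% in both arms gives 0.09 × 500 = 45.

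**4. Unadjusted test against CMH over eight strata.** Simulation, 40,000 trials per scenario. The following are assumptions, not in the documents: 35% minoritized race/ethnicity, 60% female, 45% in the heavier smoking stratum, permuted blocks of 4 within strata, and the same log-odds effect for each factor. Marginal rates were held at 9% and 18% for power, and at 9% in both arms for type I error.

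| Log-odds per factor | Type I error, unadjusted | Type I error, CMH | Power, unadjusted | Power, CMH |
|---|---|---|---|---|
| 0 | 4.9% | 4.9% | 84.4% | 84.4% |
| 0.3 | 4.9% | 5.0% | 84.6% | 84.8% |
| 0.6 | 4.7% | 5.0% | 85.0% | 85.7% |
| 1.0 | 4.4% | 4.9% | 85.1% | 86.8% |

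Monte Carlo standard errors are √(0.05 × 0.95/40,000) ≈ 0.1 points for type I error and √(0.85 × 0.15/40,000) ≈ 0.2 points for power. The row at 0.3 is therefore within noise.

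A second simulation (20,000 trials per scenario, assumed odds ratios of 0.6/0.7/0.4 and then 0.5/0.6/0.3 for the three factors) agrees. Unadjusted against CMH power was 84.6% vs 85.4% and 85.1% vs 86.3%; type I error was 4.9% vs 5.1% and 4.6% vs 5.0%.

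**The case against.** The case for leaving the plan alone is substantial.

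- **The unadjusted test is valid.** A reader might infer from the mismatch that the false-positive rate is inflated. It is not: the error goes the other way.
- **The plan is consistent with itself.** It is powered on Pearson and allows Pearson, and the 84% is right. A reader might infer that the trial is underpowered or the figure wrong. The document supports neither, and even the Fisher branch stays above 80%.
- **The gain is small and assumed.** It starts at zero and depends on prognostic strengths that the document does not give.
- **The open choice is probably harmless.** Naming both tests is common shorthand for an expected-count rule. Such a rule depends only on arm sizes and total abstainers, not on the difference between arms, so it would not favour a result, and here it would select chi-square. To infer that the test will be picked after seeing which one is significant goes beyond the text.
- **Covariate models are planned.** The interaction models must contain treatment, and the covariate list is only of examples, so cigarettes per day is not excluded.
- **A separate analysis plan, not shown, may settle all of this.**

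Most of this stands, and it limits the point to efficiency and clarity. What remains is that the article does state its primary test. That test leaves out the design factors, no selection rule is written, and the logistic models are not given the role of the adjusted treatment comparison.

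The printed smoking categories, "number of cigarettes smoked per day (20 vs ≥20", overlap at 20. A less-than sign was probably lost from the text, so this is not evidence of a fault in the randomization.

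**Conclusion.** The point holds as a modest, free improvement to a stated method. Ignoring the strata costs roughly 0 to 2 points of power (at most 1.7 in the scenarios run) and makes the test slightly conservative, with type I error of 4.4% to 4.9%. Both ranges rest on the assumed stratum shares, block size and prognostic strengths; with non-prognostic strata there is no loss. The Fisher alternative would cost about 3 points (84.6% to 81.5%, exact), but only if it were used, which is unlikely at the expected counts. The validity of the primary test, the sample size and the stated 84% are not in question.

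**What to change.** Before the arms are compared, replace the primary-test sentence so that it names one analysis: the Cochran-Mantel-Haenszel test, two-sided at 0.05, over the eight randomization strata as implemented, with a stratum-adjusted risk difference and its 95% CI. Keep the unadjusted Pearson chi-square as a supportive analysis. Delete the Fisher alternative for the primary endpoint. Do not offer a logistic model or optional covariates as an interchangeable primary analysis: a main-effects logistic model is not the same as CMH over eight cells, and offering both would reopen the choice. State the smoking stratum with the cut-off used in the randomization system.

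The cost is one or two sentences in the analysis plan. No new data are needed, and neither the sample size nor the power statement has to change.
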